Even though the definition of FGR may defer between guidelines, consistently worse perinatal outcomes of FGR fetuses with abnormal UA Doppler results have been reported compared to those with normal UA Doppler results [6–9]. Therefore, fetal vascular Doppler examinations, including UA Doppler, are important in distinguishing a pathologically growth-restricted fetus from a small but healthy fetus. Several studies predicted the perinatal outcomes of fetuses with growth restriction and these studies mainly focused on the Doppler examination of specific vessels, such as the UA, MCA, or ductus venosus (DV) [6–12]. However, besides the UA, MCA, or DV, uteroplacental-fetal circulation also consists of other components affecting fetal growth. For example, umbilical vein (UV) flow and placental thickness, which are components of uteroplacental-fetal circulation, have already been shown to be associated with fetal growth. Ferrazzi et al. reported that UV flow per unit head circumference (HC) was decreased in FGR fetuses [13]. Another study reported that venous flow was also reduced in FGR fetuses [14]. In a previous study assessing the correlation between placental thickness and small for gestational age (SGA) neonates, the placental thickness-to-EFW ratio was higher in SGA neonates compared to non-SGA neonates [15]. In addition, a thick placenta was reported to be associated with adverse perinatal outcomes [16]. In this research, we aim to focus on the uterine wall, in conjunction with the umbilical vein. The uterine wall is a distinctive aspect of this study, as it has been neglected in previous research on FGR. The causes of a thick uterine wall observed in ultrasonography are typically categorized into three main factors: sustained uterine wall contractions, adenomyosis, and uterine fibroids [17, 18]. If a thick uterine wall is observed in a pregnant woman without a history of uterine fibroids or adenomyosis, it may be attributed to a sustained uterine contraction. The uterine contractions are known to lead to a decrease in uteroplacental blood flow [18–20]. Taking this into consideration, uterine wall thickness may be associated with the uteroplacental blood flow. The hypothesis that uterine wall thickness may impact fetal growth is one of the key starting points for our research.

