Therefore, we aim to evaluate the association of UV absolute flow, placental thickness, and uterine wall thickness with adverse perinatal outcomes in the FGR fetuses, ultimately seeking to validate their involvement in the pathophysiology of FGR. In addition, we will comprehensively assess various uteroplacental-fetal biometrics and Doppler indices according to fetal growth in each trimester of pregnancy to establish a prediction model for adverse perinatal outcomes in FGR fetuses using these ultrasonographic measurements.

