### Outcomes

The primary outcome is the association of UV absolute flow, placental thickness, and uterine wall thickness with adverse perinatal outcomes in the FGR group to differentiate genuinely growth-restricted fetuses from those who are constitutionally small. The secondary outcome is to evaluate the differences in U-AID indices (UtA, UA, MCA, and UV flow, placental and uterine wall thickness, and estimated fetal body weight) between the FGR and control group will be evaluated.

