### Statistical methods

The distribution of U-AID indices according to AC, BPD, EFW and gestational age will be assessed. The study population will be divided into two groups, the FGR group which includes participants with FGR fetuses, and the control group includes participants with normal growth fetus. First of all, we will compare the differences in U-AID indices according to adverse perinatal outcomes with in FGR group. Secondly, the difference of U-AID indices between the two groups will be compared. Continuous variables will be presented as the mean ± standard deviation or median [interquartile range] and compared by the Mann-Whitney U test or independent t-test according to the distribution of each variable. Categorical variables will be presented as the number of observations (percent) and compared by the chi-squared test or Fisher’s exact test. To determine the contribution of all the collected variables and Doppler findings to adverse perinatal outcomes of the FGR fetuses, multivariable logistic regression analysis with backward stepwise elimination will be used.

All statistical analyses will be performed using IBM SPSS statistics version 23.0 (SPSS Inc., Chicago, IL, USA) and R version 4.2.1 (http://www.r-project.org).

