## Discussion

The novelty of this study lies in its comprehensive examination of all the parts within the pathway of blood flow from mother to fetus. The rationale behind this study design stems from the objective to investigate the pathophysiology of fetal growth within the clinically observable range of ultrasonography, encompassing the processes that involve UtA, uterine wall, placenta, UV and fetal growth, The aim is to elucidate the pathophysiology of fetal growth. Through this study, we aim to find the association between new ultrasonographic indices, including UV absolute flow, and placental and uterine wall thickness and perinatal outcome of growth restricted fetuses. As it is significant to distinguish growth restricted fetuses with adverse perinatal outcomes from the constitutionally small fetuses, we posit that this study may contribute to the identification of new risk factors or the development of a prediction model for genuinely growth restricted fetuses in future study. By evaluating and comparing the various ultrasonographic uteroplacental-fetal biometric measurements and Doppler indices according to fetal growth, we can determine how much each ultrasonographic index influences fetal growth. Through this finding, we can provide evidence for future studies on the pathophysiology of FGR fetuses. Lastly, we can also assess the distribution of umbilical vein flow values according to estimated fetal weight in each trimester of pregnancy.

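### The only adjusted model for the primary question takes in UV flow and EFW, which lie downstream of uterine wall and placental thickness, so it can mask the associations the study sets out to explain

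*Protocol article*

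**What the plan says.** - **Primary question** (Outcomes): "The primary outcome is the association of UV absolute flow, placental thickness, and uterine wall thickness with adverse perinatal outcomes in the FGR group".
- **Purpose.** The Introduction wants to link these three measures to disease mechanism, "ultimately seeking to validate their involvement in the pathophysiology of FGR". The same paragraph also plans a prediction model for adverse outcomes in FGR.
- **Mechanism.** The Introduction argues that a thick wall may reflect sustained contraction, that contraction lowers uteroplacental flow, and hence that "uterine wall thickness may be associated with the uteroplacental blood flow". It names an effect of wall thickness on fetal growth as a starting hypothesis. The Discussion describes the study as "encompassing the processes that involve UtA, uterine wall, placenta, UV and fetal growth".
- **Analysis** (Statistical methods). There are two steps within the FGR group. In the first, "we will compare the differences in U-AID indices according to adverse perinatal outcomes with in FGR group", with two-group tests and no adjustment. The second is the adjusted step, for which "multivariable logistic regression analysis with backward stepwise elimination will be used". Its purpose is given as follows: "To determine the contribution of all the collected variables and Doppler findings to adverse perinatal outcomes of the FGR fetuses". No confounder set is named, and the three primary exposures are not said to be kept in the model.
- **Candidates.** The Outcomes section lists the indices as "UtA, UA, MCA, and UV flow, placental and uterine wall thickness, and estimated fetal body weight"; Table 1 adds the ductus venosus.

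**The concern.** On the plan's own account, wall and placental thickness act through blood flow and growth. A logistic model that also holds UV flow and EFW estimates only the part of their effect that bypasses those routes. The closer the mechanism in the Introduction is to the truth, the closer that coefficient lies to zero.

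The fault is separate from stepwise selection: a full model, or one with the three exposures forced in, would share it. Elimination adds to it, because the variable most likely to be dropped is the one whose effect has been absorbed by its mediators.

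At stake is the reading of the study's most novel measure. A null adjusted result for wall thickness could mean no association, or an association that runs exactly as hypothesised, and the planned model cannot tell these apart. The indices nearest the outcome would take the credit.

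**Working it through.** **The plan's own figures.** The Sample size section gives 472 FGR women. That number cannot be recomputed, because no effect size, outcome rate or test is stated. The allowance for loss can be followed: 472 × 1.10 = 519.2 (stated 519), and 472 / 0.90 = 524.4, or 525 (the stated group size). Only n = 472 is carried forward. Every effect size below is an assumption.

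**Check 1: full chain.** Standardised variables follow wall W → uteroplacental flow F → UV flow U → growth G, each link with correlation p = 0.4 or 0.6:

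logit P(adverse) = −1.1 + d·W + 0.3·F + 0.3·U + 0.9·G

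Two further Doppler indices, correlated with F and G, are added as covariates. Measurement noise of SD 0 to 1 is added to the covariates other than wall, and d runs from 0 to 0.3. There are 800 runs per setting, two-sided 0.05, and backward elimination at removal p 0.10 (assumed).

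The total log-odds per SD of wall is about d + 0.3p + 0.3p² + 0.9p³. With d = 0:
- p = 0.4: 0.120 + 0.048 + 0.058 = 0.226, OR about 1.25
- p = 0.6: 0.180 + 0.108 + 0.194 = 0.482, OR about 1.62

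The fitted ORs without mediators are a little lower (1.20 and 1.48) because the odds ratio is non-collapsible. With F, U and G in the model, the wall coefficient estimates d alone, so d = 0 gives OR 1.00. The last three columns give the share of runs in which wall was significant.

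| d | p | Noise SD | OR without mediators | OR, all variables | Without mediators | All variables | After elimination |
|---|---|---|---|---|---|---|---|
| 0 | 0.4 | 0 | 1.20 | 1.00 | 43.0% | 4.9% | 7.1% |
| 0 | 0.6 | 0 | 1.48 | 1.00 | 97.9% | 5.5% | 8.9% |
| 0 | 0.4 | 1 | 1.21 | 1.08 | 42.8% | 9.0% | 13.1% |
| 0 | 0.6 | 1 | 1.47 | 1.15 | 96.2% | 19.5% | 27.8% |
| 0.2 | 0.4 | 0 | 1.41 | 1.23 | 91.5% | 36.2% | 41.5% |
| 0.2 | 0.6 | 0 | 1.75 | 1.23 | 99.9% | 29.4% | 38.6% |
| 0.3 | 0.6 | 1 | 1.88 | 1.53 | 100% | 91.4% | 94.5% |

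At least one mediator survived elimination in every run, so elimination did not undo the over-adjustment in these settings.

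**Check 2: UtA upstream.** The Discussion lists UtA before the wall, so the check was repeated with UtA as a prior variable and only UV flow and EFW as mediators (n = 472, events about 25-27%, full mediation, 1500 runs, removal p 0.10).
- Link correlation 0.4: 69% adjusting for UtA only, 6% with all variables, 6% after elimination.
- Link correlation 0.6: 64%, 4% and 8%.
- Noise SD 0.5 in both mediators: 63-70%, 6-8% and 9-12%.

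A further run with UtA upstream and a somewhat larger assumed effect gave 75-87% without UV flow and EFW. With them, under full mediation and noise-free measurement, it gave 5-6% (7-9% after elimination). With very noisy mediators or a half-direct effect it gave 23-65%.

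The result does not depend on where UtA sits. It does depend on how much of the effect is mediated and how well the mediators are measured.

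**The case against.** The case on the other side has real force.

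1. **The total association is examined.** The unadjusted comparison within FGR contains no mediators, and a mediated effect would show there. This stands, but that step cannot deal with gestational age at scan (the third-trimester window runs from 30 to 36 completed weeks) or with 13 hospitals. The 1:1 matching applies to the control group, not within FGR.
2. **Prediction is also an aim.** The primary outcome is meant to separate true restriction from constitutional smallness, and a prediction model is planned. For that, contribution beyond the other indices is a proper question. This stands, but the pathophysiological aim is stated as well and has no adjusted model of its own.
3. **Elimination changes the covariate set.** It is too strong to say that the model conditions on every other index, because only the starting model does. In the simulations of check 1, mediators nevertheless stayed in.
4. **UV absolute flow fits the argument poorly.** Wall and placenta precede it, so adjusting for them is not mediator adjustment. The Introduction itself cites UV flow scaled by head circumference, so dropping size from the UV model is contestable. This stands.
5. **The cohort is already selected on growth.** FGR requires EFW or AC, and birthweight, below the 10th percentile. That is true, but size still varies below the cut-off, so EFW adjustment can remove more signal.
6. **A condensed article leaves covariates to an analysis plan.** That would excuse silence. Here the article states the candidate set, and the stated set conflicts with a stated aim.

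**Conclusion.** The point holds as a mismatch between a stated analysis and the explanatory aim, for wall and placental thickness. The model can mask a real association. Under assumed inputs at n = 472, power drops from about 75-87% to 5-9% with full mediation and well-measured mediators, and to about 23-65% with very noisy mediators or a half-direct effect.

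A reader might infer that the plan would declare a true wall effect null, or that it has almost no power. The documents do not support this. It follows only in the extreme case, and they give no effect size, mediated share or measurement error from which to judge how near the study is to that case.

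Nor would a null in this model show that wall or placenta play no part in FGR itself. The FGR-versus-control comparison addresses that, and this regression runs within FGR only.

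The simulations assume linear chains, do not model the truncation of growth by the FGR definition, and were run for wall thickness. The extension to placental thickness rests on its place before UV flow and growth in the Discussion's account.

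**What to change.** Make one prespecified model per primary exposure the primary adjusted analysis, with the exposure forced in and adjustment for confounders only, such as maternal age, parity, gestational age at scan and centre.
- **Wall and placental models:** leave out UV flow, the fetal Doppler indices and EFW. Report with and without UtA, because the Introduction could place it after the wall and the Discussion lists it before.
- **UV flow model:** report with and without adjustment for fetal size.
- **All-variable stepwise model:** keep it as a secondary prediction analysis, and state that its coefficients are not evidence for or against an index's role in FGR.

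The cost is some wording and a few extra regressions on data already collected. The downside is more models to report, and the estimates stay conditional on the FGR restriction whatever covariates are chosen.

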### Sample size

We calculated the minimum number of FGR participants using PASS (NC, USA). Based on a published study, we set an α-error of 0.05 and a β-error of 80%, and the minimum number of FGR participants required was 472. Considering a follow-up loss rate of 10%, we need to enroll at least 519 pregnant women with FGR fetuses. Therefore, the minimum number of total participants that we anticipate including is 1,050 (525 FGR participants and 525 control participants). The researchers will first review the medical records and include eligible participants retrospectively.

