### Ultrasonographic uteroplacental-fetal biometrics and Doppler (U-AID) indices

We will collect the ultrasonographic uteroplacental-fetal biometric measurements and U-AID indices listed in Table 1 in each trimester of pregnancy. During the first trimester of pregnancy, we will collect ultrasonographic measurements from 11^0/7^ to 13^6/7^ weeks of gestation. The measurements will be assessed from 18^0/7^ to 23^6/7^ weeks of gestation during the second trimester of pregnancy and from 30^0/7^ to 36^6/7^ weeks of gestation during the third trimester of pregnancy. The ultrasound model used and the clinical experience years of clinicians who measure U-AID indices will also be documented. To assess fetal growth, crown to rump length, biparietal diameter, head circumference, abdominal circumference, femur length, and estimated body weight will be evaluated. UA Doppler which was measured in a free cord loop and MCA Doppler which was measured in the proximal third of the MCA will be selected. The systolic/diastolic ratio (S/D ratio), pulsatile index (PI), and resistive index (RI) in the UtA, UA, MCA, and UV will be calculated as reported previously [22, 23]. The Doppler indices will be calculated as follows.

S/D ratio = peak systolic velocity [cm/sec] (S)–end-diastolic velocity [cm/sec] (D)PI = S–D / mean of S and D (M)RI = S–D / SNotch index = early diastolic flow velocity [cm/sec]/ peak diastolic flow velocity [cm/sec]UV absolute flow [ml/min] = UV cross-sectional area [cm^2^] * UV mean velocity [cm/sec] * 60

**Table 1 pone.0298060.t001:** Ultrasonographic uteroplacental-fetal biometric measurements and Doppler indices of the U-AID cohort.

**Uteroplacental-fetal biometry**	**Timing of measurement**	**Unit**
Crown to rump length	First trimester	Mm
Biparietal diameter	Second trimester, Third trimester	cm
Head circumference	Second trimester, Third trimester	cm
Abdominal circumference	Second trimester, Third trimester	cm
Femur length	Second trimester, Third trimester	cm
Estimated fetal weight	Second trimester, Third trimester	g
Placental thickness	Second trimester, Third trimester	mm
Uterine wall thickness	First trimester, Second trimester, Third trimester	mm
**Uteroplacental-fetal Doppler**		**Indices**
Uterine artery	First trimester, Second trimester, Third trimester	S/D ratio, PI, RI, early diastolic notch index
Umbilical artery	Second trimester, Third trimester	S/D ratio, PI, RI
Middle cerebral artery	Second trimester, Third trimester	S/D ratio, PI, RI

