Ductus venosus	Second trimester, Third trimester	S/D ratio, PI, RI
Umbilical vein	Second trimester, Third trimester	Pulsation, cross-sectional diameter, mean velocity, absolute flow

Abbreviation: PI, pulsatile index; RI, resistive index; S/D ratio, systolic/diastolic ratio

The placental thickness and the uterine wall thickness which were measured through the sagittal section at the location of cord insertion will be collected. (Fig 1). The uterine wall was considered as a homogenous layer above the placenta.

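### In the backward-eliminated logistic model, UV absolute flow competes with the UV diameter and mean velocity it is calculated from, so the adjusted analysis can drop or misattribute a primary exposure

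*Protocol article*

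**What the plan says.** Under Outcomes: "The primary outcome is the association of UV absolute flow, placental thickness, and uterine wall thickness with adverse perinatal outcomes in the FGR group". The section on U-AID indices defines the first of these exposures by a formula: "UV absolute flow [ml/min] = UV cross-sectional area [cm^2^] * UV mean velocity [cm/sec] * 60". For the umbilical vein, Table 1 in the same section lists as collected, in the second and third trimesters: "Pulsation, cross-sectional diameter, mean velocity, absolute flow".

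Statistical methods plans two steps for the FGR group. The first is unadjusted: "First of all, we will compare the differences in U-AID indices according to adverse perinatal outcomes with in FGR group". The second is the only multivariable analysis in the article. Its purpose is given as "To determine the contribution of all the collected variables and Doppler findings to adverse perinatal outcomes of the FGR fetuses", and its method as "multivariable logistic regression analysis with backward stepwise elimination will be used". The article gives no removal threshold, no shorter list of candidates and no rule for a variable that is calculated from other candidates.

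**The concern.** Flow is a product of two other collected quantities. If area is computed from the diameter as a circle, flow is completely fixed once diameter and velocity are fixed. A model holding all three can estimate a flow coefficient only because a product is not a straight-line function of its factors. That coefficient then measures how far the product departs from linear effects of diameter and velocity. It does not measure whether UV flow is associated with adverse outcome.

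Backward elimination will often remove some of the three. Because they carry nearly the same information, sampling variation has a large say in which one remains. Two things are at stake: whether the primary exposure appears in the final adjusted model at all, and whether its odds ratio has the intended meaning when it does. The article also looks ahead to a prediction model and new risk factors, so naming the wrong UV variable would carry forward.

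**Working it through.** **Inputs from the article.** Sample size: "the minimum number of FGR participants required was 472". Error rates: "we set an α-error of 0.05 and a β-error of 80" per cent, read here as 80% power, with two-sided testing assumed. The 472 cannot be reproduced, because no effect size, event rate, standard deviation or test is given; it serves here only as n. The UV variables, the flow formula and the elimination method are as cited above.

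**Inputs assumed.** Circular cross-section; only flow affects the outcome; one trimester; three UV terms and no other covariates.
- Set A: odds ratio 0.7 per SD of flow; event rate 15, 25 or 40%; coefficients of variation (CV) for diameter/velocity of 10/20% or 15/25%; diameter and velocity independent.
- Set B: event rate 10, 20 or 40%; diameter CV 12–20%, velocity CV 25–30%; correlation 0 or 0.3. The odds ratio was set to give nominal 80% or 95% power for flow alone: OR = exp[(1.96 + z)/√(n·p·(1−p))]. This gives 1.30–1.74 per SD decrease in flow. Example at p = 20% and 80% power: (1.96 + 0.84)/√(472 × 0.16) = 2.80/8.69 = 0.322, so OR = 1.38.

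**Step 1: how redundant is flow?** Write diameter as d₀(1+a) and velocity as v₀(1+b). Flow relative to its centre is (1+a)²(1+b) = 1 + 2a + b + (2ab + a² + a²b). The part linear in diameter and velocity has variance of about 4·CVd² + CVv². The remainder has variance of about 4·CVd²·CVv² + 2·CVd⁴.
- CVs 12/25%: 0.0576 + 0.0625 = 0.1201 against 0.0036 + 0.0004 = 0.0040. R² = 0.1201/0.1241 = 0.968; variance inflation 1/(1 − 0.968) ≈ 31.
- CVs 20/30%: 0.16 + 0.09 = 0.25 against 0.0144 + 0.0032 = 0.0176. R² = 0.25/0.2676 = 0.934; variance inflation ≈ 15.

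Simulation gives the same 0.968 and 0.934. Diameter and velocity thus explain about 93–97% of the variance of flow in set B. On the log scale the three would be exactly collinear.

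**Step 2: set A, 1,500 cohorts per setting.**

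| Event rate | CVs (d/v) | Power, flow alone | Power, all three, no elimination | Flow retained, removal p>0.10 |
|---|---|---|---|---|
| 15% | 10/20% | 0.705 | 0.061 | 0.52 |
| 15% | 15/25% | 0.699 | 0.055 | 0.54 |
| 25% | 10/20% | 0.883 | 0.074 | 0.57 |
| 25% | 15/25% | 0.859 | 0.071 | 0.63 |
| 40% | 10/20% | 0.950 | 0.074 | 0.63 |
| 40% | 15/25% | 0.957 | 0.105 | 0.67 |

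Repeat runs of set A agreed. Power alone was 67–96%, and retention after elimination was 45–68% across removal at p>0.05 and p>0.10. At p>0.10, flow was the only surviving UV term in 38–55% of cohorts. Diameter and/or velocity survived with flow dropped in 30–37%.

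**Step 3: set B, 600 cohorts per setting.** Power alone was 61–95%. Flow was retained in 44–64% at p>0.05 and 51–67% at p>0.10. The like-for-like comparison, 0.05 both ways within one setting, shows a loss of 15 points (61.3% to 46.0%) to 34 points (for example 93.3% to 59.0%). At least one of the three UV terms survived in 66–95% at p>0.05. Subtracting flow's own retention setting by setting, a component stood in for flow in about 20–36% at p>0.05 and 23–37% at p>0.10.

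**The case against.** **The UV signal is mostly not lost.** Elimination usually leaves some UV term in the model, so the problem is which one is named. This stands and sets the right description: misattribution, with a material loss for flow itself.

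**Flow is also tested without its components.** The unadjusted comparison within the FGR group does this, and Outcomes speaks of an association without making an adjusted coefficient the primary test. This stands too, and confines the defect to the adjusted analysis. It does not remove the defect, because only the logistic model can show whether flow contributes beyond the other indices.

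**The modelling sentence states an aim and is not a list of terms.** Table 1 is a collection list, and a condensed article may leave the covariate list to a fuller document. Read literally, the sentence would also enter several ratios computed from the same arterial velocities. This stands in part: the final term list may be narrower. But the article does state a scope, the scope covers everything collected, and nothing narrows it.

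**Exact dependence needs area to come from the collected diameter.** The article does not say so. Diameter is, however, the only UV dimension in Table 1. A separately traced area would make the dependence strong instead of exact.

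**A stronger reading is tempting.** A reader who looks only at the three-term model, where power for flow is about 5–12% and the sign was wrong in 22–35% of set A cohorts, might infer that a real UV-flow association will nearly always be missed. The article does not support this. Those figures describe a model without elimination, whereas elimination is firmly planned and the unadjusted comparison precedes it.

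**Conclusion.** The point holds for the adjusted analysis and should be corrected. As worded, the plan lets a primary exposure compete with the quantities it is computed from. Under the assumed inputs, flow survives elimination in about 44–68% of cohorts, against about 61–96% power as the only UV term, and in roughly one cohort in three a component takes its place although flow is the sole true driver. When a component remains beside flow, the adjusted odds ratio for flow does not answer the question under Outcomes.

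The mechanism follows from the article's own formula plus the circular-area assumption. The size rests on event rates, effect sizes, measurement spread and removal thresholds that the article does not give. Other correlated candidates, such as the same index in another trimester, were not simulated and would be expected to lower retention further.

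**What to change.** Add to Statistical methods that UV cross-sectional diameter and UV mean velocity are not candidates in any model that contains UV absolute flow. State that flow is kept as the single, forced UV flow term for its primary adjusted test, and that diameter and velocity are reported descriptively or in a separate secondary model. UV pulsation is not a component of flow and is unaffected.

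Both parts are needed. Forcing flow in while the components remain would keep a coefficient with power of about 5–12% that answers a different question. Excluding the components without forcing flow would still let elimination remove a primary exposure.

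The cost is a sentence or so of text and no new data. The downside is that the separate effects of diameter and velocity move to the secondary model.
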